### Demographics

Patient demographic information will be collected at baseline (recruitment) and ICU and hospital discharge and will include; age, gender, primary reason for readmission to ICU, Acute Physiological and Chronic Health Evaluation II (APACHE II)[58], Sequential Organ Failure Assessment (SOFA) score [59], Charlson Comorbidity Index [60], time on mechanical ventilation, length of ICU and hospital stay, readmissions to ICU and 90-day mortality.

### Intervention Arm

Participants randomised to the intervention arm of the trial will undergo a specific targeted rehabilitation program prescribed by the treating ICU physiotherapist for 30 minutes, one to two times daily until discharge from the ICU within 48 hours of the diagnosis of sepsis (Early Intervention Arm). The rehabilitation program will comprise of passive or active range of motion exercises, resistive exercises, electrical muscle stimulation to major muscle groups, leg or arm ergometry, sitting out of bed, tilt table therapy and ambulation with assistance. The rehabilitation strategy for the participants in the intervention arm has been carefully planned with consideration for different levels of cardiovascular stability, ability of the patient to co-operate, and existing evidence regarding rehabilitation techniques and mobilisation strategies in intensive care. It will be administered and progressed by the discretion of the physiotherapist, according to individual acuity of illness and level of co-operation as based on the Ramsay sedation score which will account for the intervention progression stages. If the patient deteriorates, a lower level of activity will be given. Table 2 summarises the intervention strategies.

**Table 2 T2:** Intervention Strategies for early targeted rehabilitation for the critically ill.

Ramsay Sedation Scale	Stages of exercise progression	Conditions	Type of Intervention	Recommended Exercise Prescription
6-4	Stage 1	Sedated	Passive Range of Motion with stretch reflex to upper and lower limbs	30 Mins/day
			Electrical Muscle Stimulation to major muscle groups	30 Mins/day
3-2	Stage 2	Inotropic Dependence	Active Range of Motion/Lightly resisted with upper and lower limb	10 Mins × 2/day
			Electrical Muscle Stimulation to major muscle groups	30 Mins/day
			Sitting up in Bed with assistance as tolerated	30 Mins × 2/day
			Sitting on Edge of Bed	10 Mins × 2/day
2	Stage 3	Weight	Active Range of Motion/Lightly resisted with upper and lower limb	10 Mins × 2/day
		Bearing	Electrical Muscle Stimulation to major muscle groups	30 Mins/day
		Muscle Strength	Sitting On Edge of Bed	10 Mins × 2/day
		Grade < 3	Sitting Out of Bed with assistance	60 Mins × 2/day
			Lower Limb Ergometry	15 Mins × 2/day
			Tilt Table Therapy	30 Mins/day
2	Stage 4	Weight	Active Range of Motion/Lightly resisted with upper and lower limb	10 Mins × 2/day
		Bearing	Electrical muscle stimulation to major muscle groups	30 Mins/day
		Muscle Strength	Sitting On Edge of Bed	10 Mins/day
		Grade > 3	Sitting Out of Bed	30 Mins/day
			Upper Limb Ergometry (low level resistance)	15 Mins/day
			Lower Limb Ergometry	15 Mins × 2/day
			Ambulation with assistive device and therapist	30 Mins × 2/day

The Intervention strategies act as a guide for the execution of early exercises for the patients with sepsis syndromes based on the level of alertness according to the Ramsay Sedation Scale

### Control Arm

Participants allocated to the control arm will receive standard ICU care. The participants randomised to this group will not receive active rehabilitation from the research team, i.e. will not be given targeted exercises early in their disease process upon recruitment. However, they will continue to receive simple and less regular mobilisation activities from other sources, as part of the usual ICU care such as sitting out of bed or ambulation immediately prior to discharge from the unit. The time involved in these activities and the type of activities performed will be recorded and compared between groups.

### Safety and Withdrawal criteria

A safety audit will be completed on patients in the rehabilitation group to monitor any adverse events [61] during rehabilitation. Data will be gathered from the patient's IntelliVue bedside monitor MP70 (Phillips) every 10 seconds and printed out for 10 minutes prior, during and post rehabilitation. The intra-arterial line will be zeroed 10 minutes prior to exercise. A withdrawal criterion with a checklist of adverse events will be used for the clinical decision of withdrawal or modification of exercise intervention.

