## Abstract

**Background:**

Patients with sepsis syndromes in comparison to general intensive care patients can have worse outcomes for physical function, quality of life and survival. Early intensive care rehabilitation can improve the outcome in general Intensive Care Unit (ICU) patients, however no investigations have specifically looked at patients with sepsis syndromes. The 'i-PERFORM Trial' will investigate if early targeted rehabilitation is both safe and effective in patients with sepsis syndromes admitted to ICU.

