**Discussion:**

The 'i-PERFORM Trial' will determine whether early rehabilitation for patients with sepsis is effective at improving patient outcomes with functional and physiological parameters reflecting long and short-term effects of early exercise and the safety in its application in critical illness.

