### Early Rehabilitation may Modulate Detrimental Effects of Sepsis

The roles of pro-inflammatory cytokines, mitochondrial changes and muscle proteolysis in causing sepsis-induced myopathy in critically ill patients are hypothesised from animal models [6,14]. It is postulated that exercise can modulate cytokine levels [47], ROS production [50] and ATP levels [49] in patients with sepsis. In conjunction with an early mobility protocol, ambulation during mechanical ventilation in the early stages of critical illness is becoming widely practiced [50-52], especially with interruption of sedation [53-55]. Conservatively, simple passive movements [56] and neuromuscular electrical stimulation [45] as a precursor to active mobilisation can induce microcirculatory changes that may attenuate the anti-inflammatory effects in early sepsis.

Overall, early rehabilitation in critical illness seems to show reduced time on the ventilator, improved quality of life and reduced hospital and ICU stay [7] but this is not specific to sepsis. Furthermore, the short-term systemic effects of exercise for ICU patients remain highly speculative and debatable. The impact of exercise in the early stages of critical illness on effects such as oxidative stress and microcirculatory alterations have been unexplored and speculated from other populations. Exploring these physiological factors in response to exercise can contribute to determining the safety of early rehabilitation in sepsis.

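### The adverse-event audit covers only the rehabilitation arm and its sessions, so it can describe in-session tolerability but cannot compare adverse events between arms

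*Protocol article*

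**What the plan says.** The Abstract (Background) says the trial "will investigate if early targeted rehabilitation is both safe and effective in patients with sepsis syndromes admitted to ICU". Its Discussion paragraph includes, among the things the trial's measurements are to reflect, "the safety in its application in critical illness".

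Safety and Withdrawal criteria then fixes how adverse events are looked for: "A safety audit will be completed on patients in the rehabilitation group to monitor any adverse events [61] during rehabilitation". Bedside monitor data are taken "every 10 seconds and printed out for 10 minutes prior, during and post rehabilitation". The checklist has a stated purpose: "A withdrawal criterion with a checklist of adverse events will be used for the clinical decision of withdrawal or modification of exercise intervention".

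For controls, the Control Arm section describes the recording of mobilisation: "The time involved in these activities and the type of activities performed will be recorded and compared between groups". It does not mention adverse events.

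Two other places bear on safety. Demographics lists, without restriction to one arm, "time on mechanical ventilation, length of ICU and hospital stay, readmissions to ICU and 90-day mortality", together with SOFA. The section on how early rehabilitation may modulate the effects of sepsis says: "Exploring these physiological factors in response to exercise can contribute to determining the safety of early rehabilitation in sepsis".

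**The concern.** In a randomised trial, a statement that an intervention is safe normally rests on comparing harm between the arms. These patients have sepsis and have been ventilated for at least 48 hours, so many will have adverse events whatever their allocation. An audit confined to one arm cannot separate events caused by exercise from events that would have happened anyway. Background events could be blamed on rehabilitation, or a real excess could pass as the ordinary course of the illness. Adverse events arising between sessions lie outside the audit in both arms.

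This is not a detail lost in condensing the protocol. The article states the scope of the audit, and that scope does not fit the aim given in the Abstract.

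**Working it through.** The plan gives no safety figure to reproduce. The check sets the data sources side by side and then asks what each can deliver.

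**1. Sources of safety information in the article**

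| Source | Arm | Window | Stated role |
|---|---|---|---|
| Adverse-event audit and checklist | Rehabilitation only | Sessions, with monitor data 10 minutes before and after | Monitoring; withdrawing or modifying exercise |
| Mobilisation time and type | Compared between groups | Not specified | Description of activity |
| IL-6, TNF-α, IL-10 | Not restricted, but timed around the intervention | Daily in week 1, then twice weekly to ICU discharge | Secondary outcome; contributes to safety |
| mtDNA | Not restricted (a smaller number of patients) | Baseline, then weekly to ICU discharge | Secondary outcome; contributes to safety |
| Lactate | Not restricted, but timed around the intervention | Before and 30 minutes after intervention | Secondary outcome |
| 90-day mortality, ICU readmission, ventilation time, length of stay, SOFA | Not restricted | Baseline, ICU and hospital discharge; 90 days for mortality | Demographics |

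Only the first row concerns adverse events, and it has no control-arm counterpart. The last row could give a randomised comparison of harm, but no section names it as a safety outcome.

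**2. What the one-arm audit can say**

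With zero events in n treated patients, the one-sided 95% upper limit for the risk is 1 − 0.05^(1/n).

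- n = 126 (the planned number per group in Sample size): 1 − 0.05^(1/126) = 2.3%. At the 97.5% level it is 1 − 0.025^(1/126) = 2.9%.
- n = 35 (the minimum per group in Sample size): 1 − 0.05^(1/35) = 8.2%.

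These bound the risk during sessions in one arm. The control risk is not observed, so the excess over control is not estimated at any n.

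**3. What recording in both arms would add**

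The control-arm adverse-event rates here are assumptions, because the article gives none. With two-sided alpha 0.05 and 80% power, the detectable excess is:

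| Assumed control rate | 126 per arm | 35 per arm |
|---|---|---|
| 5% | 11 points | 25 points |
| 10% | 13 points | 28 points |
| 20% | 16 points | 32 points |
| 30% | 17 points | 33 points |

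**4. What 90-day mortality can say if compared by arm**

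Assumed rates are the 15%, 20% and 45% in Table 1, which states no time horizon. The 95% CI half-width for a difference is 1.96 × √(2p(1−p)/n). With n = 126:

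- p = 15%: 1.96 × √(2 × 0.15 × 0.85/126) = 8.8 points
- p = 20%: 1.96 × √(2 × 0.20 × 0.80/126) = 9.9 points
- p = 45%: 1.96 × √(2 × 0.45 × 0.55/126) = 12.3 points

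Power for a 10-point excess, with p₁ = p₀ + 0.10 and p̄ their mean, is Φ{[0.10 − 1.96√(2p̄(1−p̄)/126)] / √([p₀(1−p₀) + p₁(1−p₁)]/126)}. This gives 51%, 45% and 35% at p₀ = 15%, 20% and 45%.

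At n = 35 the half-width is 16.7 points (p = 15%) to 23.3 points (p = 45%).

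**The case against.** The strongest reply is that the article does more for safety than the audit.

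- The harms feared in the Background are oxidative stress and a worsened inflammatory reaction. Cytokines are measured to ICU discharge and mtDNA weekly, lactate is measured too, and the text gives such factors a role in judging safety.
- The monitor record begins 10 minutes before exercise, so each patient has a reference for acute haemodynamic change.
- Mortality, readmission and ventilation time are collected without restriction to one arm.
- Hypotheses and Aims contains no safety hypothesis, and no primary analysis or sample size depends on this point.
- The full protocol may contain general serious-adverse-event reporting.

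Most of this stands, and it limits the point. A reader might infer that the trial cannot answer anything about safety, that delayed inflammation goes unmeasured, or that control-arm events will not be recorded at all. The documents support none of these readings. The markers are sampled well beyond single sessions, outcomes relevant to harm are collected, and the article does not say that control events go unrecorded; it simply describes no such recording.

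The reply does not supply a between-arm adverse-event comparison. A within-patient reference shows acute change around a session, not excess risk over usual care. The markers are indirect, and the article gives no matching time anchor in controls for those timed around the intervention. Mortality and readmission can serve a safety claim only if someone designates them for it, and the article files them under Demographics.

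**Conclusion.** The point holds in a limited form. As written, the adverse-event audit supports a description of how well sessions were tolerated. It does not support the comparative safety statement implied by the Abstract. Indirect randomised evidence is available from data already planned, but it is not designated as safety evidence.

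The two-arm mortality estimate would be imprecise: about ±9 to ±12 points at assumed rates of 15% to 45%, with 35% to 51% power for a 10-point excess. This assumes all 126 per arm are observed. That number already allows for refusals, withdrawals and deaths, so the number observed may be smaller and the intervals wider. Naming mortality as a safety outcome would therefore make the claim honest and comparative, but would not by itself establish safety. The conclusion about the audit's scope rests on the text alone and on none of these assumed rates.

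**What to change.** 1. Name 90-day mortality and ICU readmission as safety outcomes, reported by randomised arm as risk differences with 95% CIs. Ventilation time and SOFA change can be added, but only with a stated rule for patients who die, because death truncates both.
2. Record adverse events in both arms from routine ICU charts, with the same definitions and the same window, from randomisation to ICU discharge. The existing checklist was written for decisions about exercise, so its items may need rewording as event definitions that apply equally to controls.
3. Keep the session audit, and label it a description of tolerability in the intervention arm.
4. If control-arm recording is not feasible, narrow the safety wording in the Abstract to in-session tolerability.

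The cost is protocol wording and modest chart abstraction for controls, with no new procedure for patients. The recording is best settled before recruitment, since control-arm events not captured during the trial may be hard to recover reliably. Treating staff cannot be blinded, so charting differences between arms remain a limitation to report.

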### Primary Outcome Measures

All primary outcomes will be measured at baseline (recruitment) and at ICU discharge and quality of life at 6 months post hospital discharge. The primary outcome measures will report the level of physical functioning and quality of life (long-term effects) of the participants. Physical function will be measured using the Acute Care Index of Function (ACIF) and the Physical Function ICU Test (PFIT).

The ACIF will essentially rate simple physical function (transfer bed to chair, sit to stand independently) of the patient on leaving the ICU [62]. The PFIT is a newly developed clinical tool for testing functional strength and endurance capacity in ICU patients. It consists of a battery of tests assessing endurance, muscle strength, cardiovascular capacity and functional ability which are domain representative of physical function and specific for the use of higher functional assessment in the critically ill [63]. These have been chosen as corresponding measuring instruments as they have demonstrated reliability, validity and responsiveness in the ICU population [63,64].

Quality of life will be measured using the Short Form-36 (SF-36) Health Survey Questionnaire. Information from the next of kin will be used to provide proxy scores which have been demonstrated to have good reliability and validity [65].

The constructs of psychological well being will be measured using the anxiety subscale of the Hospital Anxiety and Depression Scale (HADS) as psychological wellbeing is known to be highly correlated to functional physical outcomes [66].

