### Hypotheses and Aims

The primary research hypothesis of the "i-PERFORM Trial" is that patients with defined sepsis syndromes [57] in the ICU who participate in an early targeted rehabilitation program will have improved physical function and an improved quality of life. The secondary hypotheses is that there will be systemic effects underlying primary improvements which will include; increased fat free mass; decreased pro-inflammatory and increased anti-inflammatory cytokines; increased peripheral blood mitochondrial DNA content and reduced blood lactate levels; and improved tissue oxygenation and microcirculation flow.

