### Inclusion Criteria

To be eligible for recruitment in the study, participants must be aged 18 years and above; ventilated for ≥ 48 hours; diagnosed with a sepsis syndrome or have a high clinical suspicion of sepsis [57]. Patients with head injuries, burns, spinal injuries, and multiple fractured lower limbs requiring specific rehabilitation regimes and patients with septic shock who are unresponsive to maximal treatment and those who are moribund or have an expected mortality within 48 hours will be excluded.

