### Data Management and Statistical Analysis

A baseline comparison using both student t-tests and chi-square for equal proportions of demographic data will be done between groups at enrolment. Data will be analyzed using SPSS Version 17.0. The distribution, range of scores and heterogeneity will be examined for participants in both groups. Mean changes scores, standard deviations and 95% confidence intervals will be calculated and specific analysis detailed under each outcome measure will be performed. Repeated measures, between/within analysis of variance (ANOVA) will be performed to investigate for the main effects of time and group. Post hoc analyses will then be performed to ascertain where the differences occur. A Bonferroni correction will be used as the post hoc measure as there are multiple outcome measures. Analysis will be by both intention-to-treat and per-protocol method. Any violations of the protocol will be noted. Statistical significance will be set at p < 0.05 and p < 0.025(two-tailed). All efforts will be taken to avoid missing data but if it occurs a carry forward imputation will be done and linear mixed modelling will be used for overall analysis. Reasons for loss of follow up will be recorded.

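### Proxy scoring of the SF-36, a primary measure, is not limited by visit or capacity, so 6-month quality of life may not be the patient's own and change scores may mix respondents

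*Protocol article*

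**What the plan says.** Under Hypotheses and Aims, the primary hypothesis is that treated patients "will have improved physical function and an improved quality of life". Primary Outcome Measures repeats this status: "The primary outcome measures will report the level of physical functioning and quality of life (long-term effects) of the participants".

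The same section sets the visits: "All primary outcomes will be measured at baseline (recruitment) and at ICU discharge and quality of life at 6 months post hospital discharge". It also names the instrument: "Quality of life will be measured using the Short Form-36 (SF-36) Health Survey Questionnaire". Since quality of life is listed among the primary outcomes, these sentences together place the SF-36 at three visits.

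On the respondent there is one sentence: "Information from the next of kin will be used to provide proxy scores which have been demonstrated to have good reliability and validity". It names no visit, does not make the proxy conditional on the patient being unable to answer, and mentions no return to self-report.

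Inclusion Criteria fixes the patient's state at entry: "participants must be aged 18 years and above; ventilated for ≥ 48 hours".

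Data Management and Statistical Analysis says "Mean changes scores, standard deviations and 95% confidence intervals will be calculated". It adds a repeated-measures ANOVA for time and group effects, carry-forward for missing values, and a linear mixed model for the overall analysis. None of these refers to who completed the questionnaire.

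**The concern.** A proxy is close to unavoidable at recruitment, when patients have already been ventilated for two days or more. It is not unavoidable at "quality of life at 6 months post hospital discharge", when many survivors could be expected to answer for themselves. The article's sentence does not separate these situations, yet the result feeds a primary hypothesis.

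Two things are at stake. One is what the 6-month outcome means: a relative's rating is not the patient's own report. The other is what a change score measures. If the respondent changes between visits, part of the change is the difference between two raters and not a change in health.

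A further risk concerns the treatment comparison. Whether a patient can self-report at ICU discharge depends on alertness and recovery, and the intervention aims to improve recovery. The share of proxy answers could therefore differ between arms.

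**Working it through.** The plan gives no SF-36 figure to reproduce: no standard deviation, no important difference and no proxy-patient gap. The Sample size section works from the ACIF only. The check is therefore a reading of the text followed by a labelled illustration.

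**Step 1: the two readings.**

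| Reading of the respondent sentence | Recruitment | ICU discharge | 6 months | Consequence |
|---|---|---|---|---|
| A. Proxy throughout | proxy | proxy | proxy | Respondents are not mixed, but no score is the patient's own |
| B. Proxy when needed | proxy (ventilated) | mixed | mostly patient | Change may run from a proxy score to a patient score |

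The article's wording fits either row. Each has a defect, but not the same one.

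**Step 2: what a change score contains under reading B.** Let *g* be the amount by which a proxy scores lower than the patient would, and let *p* be the share of proxy answers in an arm at follow-up. With every baseline answered by proxy:

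- observed mean change = true mean change + *g* × (1 − *p*)
- bias in the between-arm difference in change (intervention minus control) = *g* × (*p*_control − *p*_intervention)

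The baseline offset is common to both arms and cancels from the second line. What remains depends only on the difference in proxy share, provided that *g* is the same in both arms.

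**Step 3: numbers.** Both inputs are assumptions: *g* = 5 or 10 SF-36 points, and the proxy shares shown.

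| Proxy share, intervention / control | Within-arm shift, *g* = 5 | Within-arm shift, *g* = 10 | Between-arm bias, *g* = 5 / 10 |
|---|---|---|---|
| 0% / 0% | 5 / 5 | 10 / 10 | 0 / 0 |
| 30% / 30% | 3.5 / 3.5 | 7 / 7 | 0 / 0 |
| 20% / 40% | 4 / 3 | 8 / 6 | 1 / 2 |
| 10% / 50% | 4.5 / 2.5 | 9 / 5 | 2 / 4 |
| 100% / 100% (reading A) | 0 / 0 | 0 / 0 | 0 / 0 |

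For proxy shares differing by 10 to 20 percentage points, the between-arm range is 5 × 0.10 = 0.5 to 10 × 0.20 = 2 points. The row with a 40-point difference shows how the figure grows under a more extreme assumption.

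**Step 4: the choice of analysis.** A change score subtracts the baseline with a fixed weight of one, which presumes that both scores are on the same footing. Using the baseline as a covariate lets the data set the weight, so a proxy baseline can serve as a predictor without being treated as the patient's own earlier score. With equal standard deviations and correlation ρ, the covariate-adjusted variance relative to that of the change score is (1 − ρ²) / [2(1 − ρ)] = (1 + ρ)/2. This is below 1 for any ρ below 1. Adjustment for baseline does not remove bias from unequal proxy shares at follow-up; that needs a respondent rule and a record of who answered.

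The carry-forward rule adds one detail: it could place an earlier, possibly proxy, score in the 6-month slot.

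**The case against.** **It is an article, and the full protocol may hold the rule.** Respondent-by-visit detail often sits in the full protocol or the data-collection manual, and its absence from an article would be no finding. This limits the point, but does not remove it: the article makes a positive, unqualified statement about how a primary measure is scored. If a limit exists elsewhere, the published sentence still misstates it.

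**The text does not say that respondents are mixed.** This stands. A reader might infer that change scores will combine proxy and patient answers, or that patients will never self-report. The article states neither. Only *may* is supported.

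**A common offset cancels between arms.** This also stands. A reader might take the 5 to 10 points as bias in the treatment effect. It is a within-arm shift and leaves the randomised contrast untouched when proxy use and proxy error are equal across arms.

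**The remaining bias is small and assumed.** This stands too. Nothing in the documents shows that 0.5 to 2 points would matter, and the article cites a source for proxy reliability and validity that cannot be checked here. Even so, validity of proxy scores in general does not make proxy and patient answers interchangeable within one change score.

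**Primary status is uneven.** The Abstract ties its primary measures at ICU discharge to the ACIF and PFIT. The hypothesis and the outcomes section nevertheless both count quality of life as primary.

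**A self-report-only analysis selects on a post-randomisation trait.** This is correct, so that analysis can only be supportive.

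**Conclusion.** The point holds in a limited form. As written, either 6-month quality of life is proxy-rated even for survivors able to answer, or change scores may run from a proxy baseline to a patient's later answer. In the second case, within-arm change and the time effect include the proxy-patient difference.

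The documents do not show that the treatment comparison is biased. That would need proxy use or proxy error to differ by arm. A difference in use is plausible at ICU discharge, but it is an inference. The figure of 0.5 to 2 points is an illustration from an assumed gap of 5 to 10 points and an assumed difference in proxy share of 10 to 20 percentage points. It is not an estimate for this trial.

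The change is worth making because it is cheap, concerns a primary measure, and depends on recording respondent type during collection, as this may not be recoverable later.

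**What to change.** **Primary Outcome Measures.** State the respondent at each visit:

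- Recruitment: the proxy answers.
- ICU discharge: the patient answers if able, otherwise the proxy.
- 6 months: the patient answers whenever able, and the proxy only if the patient is unable.
- Every visit: record who answered.

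**Data Management and Statistical Analysis.** Base the between-arm quality-of-life result on the 6-month score with the baseline score as a covariate, or the equivalent contrast in the linear mixed model already named. Do not base it on a change score across respondents. Report the proxy share by arm at each visit. As sensitivity analyses, adjust for respondent type and also show self-reports only. State that ability to self-report arises after randomisation, so both are supportive only.

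**Cost.** Protocol wording, one field on the questionnaire and a small extra analysis. No added visits or staff.
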